### Interim analyses {21b}

No interim analyses are planned.

### Methods for additional analyses (e.g. subgroup analyses) {20b}

Diagnosis-specific effects will be examined using mixed-effect models extended by the interaction effect of time × treatment × diagnosis group. In addition, effects of GBV intensity on primary and secondary outcomes will be examined.. In-depth analysis should reveal effects of specific features of the GBV teams (e.g. peer-led teams, attitudes, recovery orientation, and interprofessional collaboration).

### Methods in analysis to handle protocol non-adherence and any statistical methods to handle missing data {20c}

In addition to the main analysis, a per-protocol (PP) approach will be followed to analyse the primary outcome in order to assess the maximal intervention efficacy in ideal conditions based on comparable outcome measurements. Criteria for the PP population will be defined in the statistical analysis plan prior to data analysis and may include
More than 2 months between baseline assessment (*t*_0_) and initial meeting with the GBV team for participants in the intervention groupNoncompliance with or infrequent use of GBV by participants in the intervention groupFollow-up assessments (*t*_1_, *t*_2_, *t*_3_, and *t*_4_) being far outside the initially planned time periods (more than 2 months before or after the intended time points: 6 months, 12 months, 18 months, and 24 months after baseline assessment *t*_0_)

No imputation of missing data will be needed for the main analysis via mixed linear models. For the sensitivity analysis, missing values will be handled using the multiple imputations method [29]. Missing data will be imputed ten times. Then, each of the completed datasets will be analysed using the proposed statistical method. According to Rubin’s rule, the final result will be the average result of all completed datasets.

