### Criteria for discontinuing or modifying allocated interventions {11b}

GBV is a complex mental health care programme and follows a need-adapted approach. Consequently, the intervention varies between patients and over time depending on the patients’ current mental health state and preferences.

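### The candidate per-protocol exclusions act on the GBV arm only and treat need-adapted low use as non-adherence, so if adopted the analysis is not a randomised comparison and cannot show maximal efficacy

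*Protocol article*

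**What the plan says.** Section {20c} of the protocol article commits to a supplementary analysis: "a per-protocol (PP) approach will be followed to analyse the primary outcome in order to assess the maximal intervention efficacy in ideal conditions". The population is not yet final: "Criteria for the PP population will be defined in the statistical analysis plan prior to data analysis and may include" three listed items.

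- More than 2 months between baseline and the "initial meeting with the GBV team for participants in the intervention" group.
- Noncompliance with GBV, or "infrequent use of GBV by participants in the intervention" group.
- Follow-up visits "more than 2 months before or after the intended time points".

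The first two are worded for the intervention group. The third applies to both groups.

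On the intervention itself, section {11b} says that "the intervention varies between patients and over time depending on the patients’ current mental health state and preferences". The case management paragraph of {11a} ties contact frequency to need, and section {30} makes months 19 to 24 a phase of transfer to CAU. Section {6b} gives controls no access to GBV services. Section {20b} adds that "effects of GBV intensity on primary and secondary outcomes will be examined", without stating a method. Section {20a} makes intention-to-treat mixed models the main analysis.

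**The concern.** A per-protocol population keeps the protection of randomisation only if retention is unrelated to outcome or works alike in both arms. Neither can be expected here. A control cannot be an infrequent user of GBV or be late for a first GBV meeting, so these two rules thin out one arm only, on events after allocation.

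The use rule has a further problem. GBV is meant to be used more or less according to how the patient is doing. Some low users have improved and need little; others have disengaged while ill. Removing the first kind understates GBV, and removing the second kind flatters it. The label given to the analysis implies an upper bound on what GBV can achieve, and nothing in the construction secures one. The Discussion says the trial will inform financing by the statutory health insurance, so a per-protocol figure carrying that label could be misread.

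The intensity analysis faces the same dependence: if patients with more need receive more GBV, intensity and outcome are associated whatever GBV does.

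**Working it through.** **Which arm each rule can touch.** Late first meeting: GBV only. Noncompliance or infrequent use: GBV only, since {6b} bars controls from GBV. Off-schedule visits: both arms.

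**Whether low use is a deviation.** Under {11a}, {11b} and {30}, low use can reflect low need, preference or the planned transfer phase. Frequency of use alone therefore does not separate non-adherence from GBV as designed.

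**Inputs from the plan.** The article states no figure for the per-protocol analysis. Two figures from {14} serve as a yardstick:
- Planned effect at t4: 0.20 SD.
- Retention at t4: 1 − 0.15 − 0.07 − 0.04 − 0.02 = 0.72, as stated. With 1000 patients allocated 1:1, this is 0.72 × 500 = 360 per arm.

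**Assumed inputs.** The article gives no usage rates and no link between use and EPAS change. Let q be the share of the GBV arm excluded (10–30%) and r the correlation between GBV use and the patient's own 24-month change (−0.3 to +0.3). A positive r means heavier users improve more.

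**Simple form.** Shift of the retained mean against the full arm = q × (retained mean − excluded mean). With q = 0.2 and a gap of 0.2 SD: 0.2 × 0.2 = 0.04 SD. With q = 0.3 and a gap of 0.5 SD: 0.3 × 0.5 = 0.15 SD.

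**Truncation form.** If the lowest share q of users is dropped and use and change are jointly normal, the shift is r × φ(c)/(1 − q), where c is the q-quantile of the standard normal. For q = 0.2, φ(c)/(1 − q) = 0.280/0.8 = 0.350. With no true GBV effect, in SD of change:

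| q | r = ±0.1 | r = ±0.2 | r = ±0.3 |
|---|---|---|---|
| 10% | ±0.019 | ±0.039 | ±0.058 |
| 20% | ±0.035 | ±0.070 | ±0.105 |
| 30% | ±0.050 | ±0.099 | ±0.149 |

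**Simulation.** 360 per arm before exclusion, 4000 runs, two-sided 5% level (assumed; the article states no alpha), simple comparison of mean change:
- No true effect, r = 0: no bias; rejection rate 4.9–5.4%.
- No true effect, r = ±0.2, q = 20%: rejection rate 13.6–14.9%.
- No true effect, r = ±0.3, q = 30%: rejection rate about 45%.
- True effect 0.20 SD, q = 30%: mean estimate 0.05 at r = −0.3 and 0.35 at r = +0.3.

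**Intensity.** With no GBV effect, an unadjusted regression of change on use within the GBV arm returned a standardised slope equal to r (about ±0.20 and ±0.30 in simulation).

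**The case against.** The strongest reply is that nothing has been fixed. Section {20c} says the criteria may include these items and leaves the definition, including any threshold for infrequent use, to an analysis plan that is not shown. A reader might infer that the trial will drop infrequent users; the article does not say so. This stands, and the point is conditional on adoption. It survives because the article does fix the purpose of the analysis and the one-arm nature of the listed rules, and a sharper threshold would not cure either.

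Second, the protocol has requirements that do not depend on need: service plans are reviewed at least every 6 months ({11a}, service planning), and the intervention starts straight after baseline and allocation ({13}). Non-adherence could be defined against these, and a 2-month delay is a real departure rather than need-adapted delivery. That is fair. The argument from need adaptation bears on the use rule; the delay rule is open only to the objection that it selects after randomisation in one arm.

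Third, a reader might infer that the intensity analysis is confounded as planned. The article gives no method, so confounding by need is a risk built into the design and not a shown omission.

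Fourth, the magnitudes only restate the assumed inputs. That is true of both calculations.

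**Conclusion.** The point holds in conditional form. If the two GBV-only criteria are adopted, the per-protocol result compares a selected GBV group with all CAU patients. The bias can go either way, so the result is not an upper bound and does not support the maximal-efficacy label.

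Its size and sign cannot be derived from the article. Under the assumed ranges it runs from nothing (r = 0) to about 0.15 SD. That equals 0.15/0.20 = 75% of the planned effect if the SD of change and the SD behind the planned 0.20 are similar, which the article does not say.

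Two stronger readings are not supported. The trial's main conclusion is not endangered: it rests on the intention-to-treat analysis, which these criteria do not touch. Nor can it be said that the per-protocol analysis would favour GBV, because excluding patients who use little since they are well would work against it.

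**What to change.** 1. Do not use frequency of GBV use as an exclusion criterion.
2. Estimate the supplementary efficacy effect on EPAS as a complier-average causal effect, with randomisation as the instrument and all randomised patients kept in their arms. Because controls have no access to GBV, non-compliance is essentially one-sided, and in its simplest form the estimate is the intention-to-treat effect divided by the proportion of the GBV arm that takes up GBV.
3. Define compliance as taking up GBV at all, for example attending the initial meeting, and fix this before unblinding. A minimum-use threshold would not serve: patients below it still receive GBV and can call on the crisis service ({11a}), so allocation could affect them, which violates the exclusion restriction.
4. Apply any visit-timing rule identically in both arms.
5. Drop the maximal-efficacy label from any per-protocol result that is kept.
6. Report the intensity analysis in {20b} as an exploratory association, since intensity follows need by design.

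The cost is wording in the analysis plan and one standard instrumental-variable analysis, with attendance at the initial meeting recorded. The downsides are wider intervals and reliance on the untestable assumption that allocation affects empowerment only through GBV uptake.

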### Sample size {14}

The calculation of the expected effect size is based on the results of a previous study (IVPOWER) [10]. Since the total score of the scale for measuring empowerment in patients with affective and schizophrenic disorders (EPAS) as the primary outcome proved to be rather difficult and slow to change, a low effect size of 0.20 and a high power of 0.90 were chosen for the sample size calculation of the present study.

The sample size calculation was based on a linear mixed-effects regression model with an interaction effect between study group and measurement time. The expected effect size, alpha value, beta value, number of measurements, number of study sites, and expected number of dropouts over all follow-up measurements were taken into account.

Based on the results of the IVPOWER study, an increase in the effect size of the primary outcome parameter is expected, from 0 standard deviations (SD) at baseline (*t*_0_) to 0.2 SD at the last assessment (*t*_4_). Furthermore, a decreasing dropout rate of 15% between *t*_0_ and *t*_1_, 7% between *t*_1_ and *t*_2_, 4% between *t*_2_ and *t*_3_, and 2% between t_3_ and t_4_ is expected, so that the expected sample size at *t*_4_ still comprises 72% of the initial sample.

A sample size calculation using the Web-based programme RMASS (www.rmass.org) yielded a number of at least 978 subjects for twelve study sites. On this basis, the target sample size was set at 1000 participants.

We expect to include about 350 informal caregivers, of whom about 225 will complete the study based on the experience gained in the IVPOWER study (recruitment rate = 36.8%; dropout rate = 35.6%).

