## Statistical methods

### Statistical methods for primary and secondary outcomes {20a}

The data will be managed using IBM SPSS 25 and analysed using STATA 15 and SAS 9.4.

In order to evaluate the indication for GBV, the interrater reliability will be determined (using Spearman rank correlation) for the EPAS, HoNOS, and CAN ratings between screenings carried out by GBV team members and the baseline assessments carried out by local research workers. Furthermore, the criteria for serious mental illness will be assessed in the baseline data, and descriptive statistics will provide information on whether the target population has been recruited.

The analyses of primary and secondary outcomes will follow the intention-to-treat (ITT) principle using mixed-effects models with random time effects and time × treatment interaction effects. The covariance structure will take the study sites and individuals into account.

The cost-effectiveness ratios will be determined using the net benefit method, from the perspectives of both the statutory health insurance and national economy.

The implementation of GBV at the study sites will mainly be evaluated using descriptive methods. Mediator and moderator analysis will be conducted for the process variables, such as recovery orientation and multiprofessional collaboration.

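### The stated missing-data sensitivity analysis rests on essentially the same missing-at-random assumption as the main mixed model, so it cannot test robustness to outcome-related dropout

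*Protocol article*

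**What the plan says.** Protocol article, section {20c} (non-adherence and missing data), sets out the missing-data strategy in four steps:

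- Main analysis: "No imputation of missing data will be needed for the main analysis via mixed linear models".
- Sensitivity analysis: "For the sensitivity analysis, missing values will be handled using the multiple imputations method".
- Number and analysis of imputations: "Missing data will be imputed ten times", after which "each of the completed datasets will be analysed using the proposed statistical method".
- Combination: "According to Rubin’s rule, the final result will be the average result of all completed datasets".

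Section {20a} describes the main analysis as intention-to-treat, using "mixed-effects models with random time effects and time × treatment interaction effects". The only other supplementary analysis of the primary outcome in {20c} is per-protocol, which concerns adherence and visit timing. The missing-data assumption is not named. No delta-adjusted, tipping-point, reference-based or other missing-not-at-random analysis is mentioned.

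Sample size {14} expects that the sample at t4 "still comprises 72% of the initial sample".

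**The concern.** A sensitivity analysis for missing data should vary the assumption on which the main result depends. A likelihood-based mixed model is valid when dropout is MAR given the observed data. Multiple imputation with no stated departure from MAR, followed by the same mixed model, targets the same quantity under essentially the same condition. The two results should be close whether or not MAR holds, so their agreement would be weak evidence of robustness.

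MAR is open to doubt in this design. Participants, providers and data collectors are unblinded (section {17a}), and EPAS is a self-assessment (section {18a}). Only the GBV arm has continuous contact with a case manager. The CAU arm consists of people assessed as needing GBV who then have no access to it. Dropout related to current empowerment, and different between arms, is therefore plausible. The target effect is small (0.20 SD) relative to the expected loss (28%), so a moderate departure in one arm could change the primary conclusion, and the check as stated would not show it.

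**Working it through.** **Inputs from the article.** Dropout by interval is 15%, 7%, 4% and 2%. The effect grows from 0 to 0.20 SD at t4. Power is 0.90, the calculated sample size 978, the target 1000, and allocation 1:1 (Sample size {14}; Trial design {8}).

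**Assumptions made here.** Two-sided alpha is 0.05, since {14} names alpha as an input but gives no value. Dropout is equal in both arms. The departures δ have no source in the documents. The standard error is held fixed as δ varies.

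**Step 1: the plan's own figure.** 1 − (0.15 + 0.07 + 0.04 + 0.02) = 0.72. The stated 72% is reproduced when the rates are read as shares of the initial sample, leaving 28% missing at t4. Compounded rates would give 0.85 × 0.93 × 0.96 × 0.98 = 0.744, or 25.6% missing.

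**Step 2: what each analysis assumes.**

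| | Main analysis | Sensitivity analysis as stated |
|---|---|---|
| Missing values | left missing; likelihood on observed data | imputed ten times |
| Departure from MAR | none | none stated |
| Model fitted | mixed model | the same mixed model |

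The imputation model is not given. If it includes auxiliary variables, MAR becomes more plausible, but departures from it remain untested.

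**Step 3: size of a departure.** Let δ be the amount, in SD of EPAS, by which dropouts in an arm are worse at t4 than MAR predicts. With a fraction 0.28 missing in each arm,

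t4 difference = 0.20 − 0.28 × (δ_GBV − δ_CAU).

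| δ_GBV | δ_CAU | t4 difference (SD) |
|---|---|---|
| 0 | 0 | 0.200 |
| 0.1 | 0 | 0.172 |
| 0.2 | 0 | 0.144 |
| 0.3 | 0 | 0.116 |
| 0.5 | 0 | 0.060 |
| 0.3 | 0.3 | 0.200 |
| 0 | 0.3 | 0.284 |

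At δ = 0.3 in GBV only, the loss is 0.084 / 0.20 = 42% of the target effect; at 0.5 it is 0.14 / 0.20 = 70%. The difference reaches zero at 0.20 / 0.28 ≈ 0.71 SD.

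**Step 4: where significance is lost.** The standard error implied by the plan, scaled to 1000 participants, is 0.20 / (1.960 + 1.282) × √(978/1000) ≈ 0.061. The smallest significant difference is 1.960 × 0.061 ≈ 0.120. Setting 0.20 − 0.28 × δ = 0.120 gives δ ≈ 0.080 / 0.28 ≈ 0.29 SD, for a departure in GBV only. With 25.6% missing it would be 0.080 / 0.256 ≈ 0.31 SD.

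This is arithmetic on the t4 contrast. The shift in a fitted time × treatment coefficient would also depend on when participants leave and how time is modelled.

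**The case against.** **The statistical analysis plan is not shown.** Imputation models, auxiliary variables and delta ranges often belong there, and the article is a condensed account. This stands to the extent that no claim can be made about the whole plan, only about what the article states. It does not remove the point. Section {20c} defers the per-protocol criteria to the analysis plan, but it specifies the missing-data sensitivity analysis itself, and that choice can be reviewed.

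**Multiple imputation need not reproduce the mixed model.** With auxiliary variables it can rest on a weaker form of MAR. This also stands: it would be too strong to say that the imputed analysis must return the main estimate plus simulation noise. It would still not examine dropout that depends on unobserved EPAS.

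**The illustration is one-sided.** The deltas are unsourced, equal departures in both arms cancel, and if CAU dropouts are the worse group the MAR estimate understates GBV. All of this is correct. It is a reason to vary δ separately by arm, not evidence that the result is biased in a known direction.

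**Pooling.** A reader might infer from "the final result will be the average result of all completed datasets" that between-imputation variance will be omitted and standard errors will be too small. The text does not support that. The sentence invokes Rubin's rule, averaging is that rule's step for the point estimate, and the rule itself supplies the between-imputation part of the variance. The wording is brief, but it states no error.

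**Ten imputations.** A reader might also call ten too few. At an assumed missing-information fraction of 0.20 to 0.28, the standard error is inflated by √(1 + 0.20/10) to √(1 + 0.28/10), about 1.0% to 1.4%. A larger number is a preference, not a correction.

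**Conclusion.** The point holds for what the article states. Its missing-data sensitivity analysis shares the main model's MAR assumption in all essentials and cannot test robustness to outcome-related dropout. The primary analysis itself is not in error, and no bias has been shown.

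The point matters because the target effect is small and the expected loss large. A departure of about 0.29 SD confined to GBV dropouts would take a 0.20 SD effect out of significance, given two-sided 5%, a standard error of about 0.061, equal dropout by arm and 28% missing at t4. Those figures show how sensitive the conclusion could be; they do not predict what will happen. The change should be made, because a statement of robustness based on the present check would not be supported by it.

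**What to change.** Name MAR as the assumption of the main mixed model. Keep the planned multiple imputation and build on it:

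- Add a delta-adjusted (tipping-point) analysis of EPAS. Shift imputed values by δ, separately for GBV and CAU, over a prespecified range such as 0 to 0.5 SD in each arm.
- Report the treatment effect and its interval across the two-way grid, and state which combinations change the primary conclusion.
- Include auxiliary data already collected in the imputation model. Candidates are the screening EPAS, CAN and HoNOS scores and, where consent covers them, health insurance data. Say that these support MAR and do not test it.

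The cost is some wording in the analysis plan and modest programming. Randomisation, visits, sample size and the primary analysis are unaffected. The downside is that the robustness statement may be less favourable than one based on MAR imputation alone.

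### Ten imputations are valid, but they leave a borderline p-value in the missing-data sensitivity analysis noticeably dependent on the random draw; at least 50 would largely remove this for the price of computing time

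*Protocol article*

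**What the plan says.** The section on non-adherence and missing data ({20c}) of the protocol article separates two analyses. For the primary one it says: "No imputation of missing data will be needed for the main analysis via mixed linear models". For the supportive one it says: "For the sensitivity analysis, missing values will be handled using the multiple imputations method". It then fixes the number, "Missing data will be imputed ten times", and the pooling: "According to Rubin’s rule, the final result will be the average result of all completed datasets".

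The sample-size section ({14}) expects stepwise dropout of 15%, 7%, 4% and 2%, so that the sample at t4 "still comprises 72% of the initial sample". It plans for a small effect: "a low effect size of 0.20 and a high power of 0.90 were chosen". It says that an alpha value entered the calculation but does not print it, and it gives no correlation between visits.

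**The concern.** Multiple imputation uses random draws, so with a finite number of imputations the pooled estimate, its standard error and its p-value all depend partly on the seed. The dependence grows with the share of information that is missing and shrinks with the number of imputations. More than a quarter of participants are expected to be missing at t4, and this is the only missing-data sensitivity analysis that the article describes. Its purpose is to show whether the main result holds up under another treatment of the missing values. If the two analyses appear to disagree, the reader should be able to attribute that to the handling of missing data and not to the draw. Because the number is stated in the article, it is not a detail left open for the analysis plan.

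**Working it through.** **Inputs from the article.** Ten imputations (section {20c}); dropout of 15%, 7%, 4% and 2%, and 72% retention at t4 (section {14}); five visits at 6-month intervals; analysis by mixed models with a time × treatment interaction.

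**Assumptions, because the article gives no figure.** Correlation between visits of 0.3 to 0.8, with compound symmetry or AR(1) structure; two-sided 5% level.

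**Step 1: retention.** 100 − 15 − 7 − 4 − 2 = 72%, which is the article's figure, so the rates are shares of the initial sample. (Taken as conditional rates they would give 0.85 × 0.93 × 0.96 × 0.98 = 74.4%.) Cumulative missingness at t1 to t4 is 15%, 22%, 26% and 28%.

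**Step 2: fraction of missing information (FMI).** FMI = 1 − (variance of the slope contrast with complete data) / (variance with the stated dropout), by generalised least squares:

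| Correlation | Compound symmetry | AR(1) |
|---|---|---|
| 0.3 | 0.204 | 0.157 |
| 0.5 | 0.223 | 0.161 |
| 0.6 | 0.231 | 0.167 |
| 0.7 | 0.239 | 0.176 |
| 0.8 | 0.246 | 0.188 |

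The range is about 0.16 to 0.25. It lies below 0.28 because most participants who are missing at t4 contribute at least their baseline, and some contribute later visits.

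**Step 3: efficiency and noise of the estimate with m imputations.** Relative efficiency = 1/(1 + FMI/m). At FMI 0.20 and m = 10 this is 1/1.02 = 0.980. The Monte Carlo SD of the pooled estimate, in standard errors, is √(FMI/m) = √(0.20/10) = 0.141. At m = 50 it is 0.063.

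**Step 4: spread of the p-value over draws.** Scale the limiting variance to 1, with within-imputation variance W = 1 − FMI and between-imputation variance B = FMI. For each draw, the pooled z is normal around its limiting value with variance FMI/m. The estimated B is FMI × χ²(m−1)/(m−1). Rubin's total variance is T = W + (1 + 1/m)B, and p comes from a t distribution with (m−1)[1 + W/((1 + 1/m)B)]² degrees of freedom. The limiting p is the value approached as m becomes large.

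| FMI | m | Central 95% of p when limiting p = 0.05 | Chance that limiting p = 0.03 shows as >0.05 |
|---|---|---|---|
| 0.15 | 10 | 0.026 to 0.096 | 10.1% |
| 0.15 | 50 | 0.038 to 0.067 | 0.1% |
| 0.20 | 10 | 0.023 to 0.109 | 15.5% |
| 0.20 | 50 | 0.036 to 0.070 | 0.4% |
| 0.20 | 100 | 0.039 to 0.064 | <0.1% |
| 0.28 | 10 | 0.019 to 0.129 | 23.1% |
| 0.28 | 50 | 0.033 to 0.076 | 1.8% |
| 0.28 | 100 | 0.037 to 0.067 | 0.1% |

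The rows at 0.15 and 0.28 bracket the derived FMI. At its upper end, 0.25, the same calculation with m = 10 gives 0.020 to 0.122 and 20%; with m = 50 the second figure is about 1%. A limiting p of 0.01 shows as >0.05 in about 1% of draws at most (FMI 0.28, m = 10).

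**Hand check of the 15.5%** (FMI 0.20, m = 10). Typical T = 0.80 + 1.1 × 0.20 = 1.02. Degrees of freedom are 9 × (1 + 0.80/0.22)² ≈ 193, so the critical t is 1.972. The pooled z must exceed 1.972 × √1.02 ≈ 1.992. A limiting p of 0.03 is z = 2.170, a gap of 0.178. The noise combines 0.141 from the estimate with about 0.101 from the standard error: 1.972 × 0.22 × √(2/9) / (2 × 1.01). Together √(0.141² + 0.101²) ≈ 0.174. Then 0.178/0.174 ≈ 1.02 SD, a tail of about 15%.

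**The case against.** The strongest reply is that nothing here is an error.

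- **Validity.** Rubin's variance and degrees of freedom allow for a finite number of imputations, so intervals and p-values are valid at ten, with 97 to 98% efficiency. This stands. A reader might infer that ten is too few in the sense of giving wrong inference; the documents do not support that. Nor does the sentence that describes pooling as an average show that the variance will be pooled wrongly, since it invokes Rubin's rule.
- **Consequences.** The primary conclusion rests on a mixed model without imputation, and the article attaches no 5% decision to the sensitivity analysis. This stands too. Read as an estimate, the noise is trivial. With an effect of 0.20 SD and 90% power at two-sided 5%, the standard error is about 0.2/(1.960 + 1.282) = 0.062 SD, and 0.15 of that is about 0.009 SD.
- **Likelihood.** Under the planned effect the expected z is about 3.24. Only about 11% of trials would fall between z = 1.66 and 2.26, where the issue matters most. This limits how often the weakness would matter; it does not remove it.
- **The 28%.** A reader might take 28% missing at t4 as 28% of the information missing. That overstates it, as step 2 shows.
- **Reproducibility.** A reader might say that a re-run would not reproduce the result. With the same code and seed it would. The article offers code on request, and seed and Monte Carlo error reporting are ordinary analysis-plan content, so their absence from the article is no fault. A recorded seed makes one draw repeatable, however; it does not make that draw typical.
- **Residual noise.** Some dependence on the draw remains at any finite number, including 100. True, but it is much smaller.

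**Conclusion.** The point holds as a minor one about stability. With the stated dropout and ten imputations, a borderline sensitivity result depends noticeably on the draw: a limiting p of 0.05 ranges over about 0.02 to 0.12, and a limiting p of 0.03 appears above 0.05 in about 10 to 20% of draws. Results near 0.01 are not affected in practice.

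These figures rest on three assumptions that the article does not settle: visit correlations of 0.3 to 0.8 under compound symmetry or AR(1), a two-sided 5% reading of the sensitivity analysis, and dropout as forecast. The primary analysis is not touched. The case for acting is that the number is written into the article and a better one is almost free.

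**What to change.** In section {20c}, and in the analysis plan if it repeats the number, replace ten imputations with at least 50; 100 is also fine. At 50, the chance that a limiting p of 0.03 appears above 0.05 falls to about 1% or less over the derived range of missing information. The only downside is computing time; the design, sample size, data collection and primary analysis stay as they are.
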